#### Food consumption

Food consumption will be assessed by means of three 24-h food recalls undertaken on separate days (i.e., 2 weekdays and 1 weekend day), using a visual aid photo album of real foods, which consists of listing all foods and beverages consumed during the prior 24 h. Patients will be instructed to maintain the same diet throughout the study. Energy (kilocalories) and macronutrient (grams and total percentage) intake will be calculated by a trained nutritionist using Dietbox® software (online version).

#### Mechanistic analyses

##### Skeletal muscle biopsy

Percutaneous muscle biopsies will be performed in a random sub-sample of 20 patients at PRE and POST, immediately after the oral glucose tolerance test. In brief, muscle biopsies will be obtained under local anesthesia (2–3 mL of 1% xylocaine) from the muscle vastus lateralis, using a 5-mm Allendale needle with suction. Immediately after the biopsy procedure, the sample will be blotted dry and trimmed of visible adipose and connective tissue using a standard dissecting microscope. Four portions of the specimen (~ 30–100 mg) will be snap frozen in liquid nitrogen and stored at − 80 °C.

##### Non-targeted analysis

We will perform RNA sequencing (RNA-seq; Fig. 5). Total RNA will be extracted, homogenized from ~ 20 mg of muscle tissue using TRIzol reagent (Invitrogen®), and isolated according to the RNeasy Fibrous Tissue Mini Kit (Qiagen®) protocol, using a Kinematica™ Polytron™ PT 1300 (FisherScientific®). Total RNA will be determined spectrophotometrically at 260 nm (GE Healthcare®) and RNA integrity number (RIN) will be checked by capillary electrophoresis using a Bionalyzer 2100 (Agilent®). For each sample, ~ 3 ul of total RNA extract will be delivered to the Pennington Biomedical Research Center Genomics Core for RNA sequencing (RNA-seq) analysis. Sample concentration will be normalized and complementary DNA (cDNA) pools will be created for each sample, and subsequently tagged with a barcoded oligo adapter to allow for sample-specific resolution. Sequencing will be carried out using an Illumina HiSeq 2500 platform (Illumina®) with a 50-bp single end reads. The quality of RNA-seq data will be checked using FastQC v0.10.0 (Barbraham Bioinformatics®). Alignment to the reference genome (rn5, UCSC), differential expression based on counts per million mapped reads (CPM), and post-analysis diagnostics will be carried out. RNA-seq data will be deposited in National Institutes of Health Gene Expression Omnibus (NIH GEO) and normalized CPM values for all measured genes will also be provided. To validate the RNA-seq data, gene and protein expression will be then determined by quantitative real-time PCR (qRT-PCR) and western blotting, as described in the following sections.

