### Patient recruitment and selection

Patient recruitment and selection will take place at the Clinical Hospital (School of Medicine, University of Sao Paulo). Postmenopausal patients diagnosed with rheumatoid arthritis (*N* = 30) [32] will be recruited directly from the Rheumatoid Arthritis Outpatient Clinic of the Rheumatology Division. The exclusion criteria include (1) participation in structured exercise training programs within the last 12 months; (2) unstable drug therapy in the last 3 months prior to and during the study; (3) Health Assessment Questionnaire score > 2.0 (i.e., severe physical impairment).

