##### Targeted analyses

Gene expression will be determined by qRT-PCR (Fig. 5). In brief, total RNA isolation, quantification, and purity will be carried out as described above. Gene expression will be determined by qRT-PCR analyses using the microglobulin (*B2M*) gene as a housekeeping gene. All qRT-PCR reaction mixtures will be prepared using a Superscript Platinum One-Step kit (Invitrogen, CA, USA) with incorporated Maxima SYBR Green/ROX qPCR Master Mix (Applied Biosystems, CA, USA) on a Step One Thermocycler (Applied Biosystems, CA, USA). The messenger RNA (mRNA) levels of the genes lipoprotein lipase (*LPL*), pyruvate dehydrogenase kinase 4 (*PDK4*), and aetyl-CoA carboxylase alpha (*ACACA*) will be analyzed. Potential genes that emerge from the RNA-seq analysis will be validated using qRT-PCR analysis. Relative change in gene expression (Δ-ΔCq) will be calculated by subtraction of the ΔCq at PRE (used as a calibrator) to the corresponding ΔCq at POST. Finally, fold change will be determined as 2-Δ-ΔCq. All sense and reverse primers used for each gene will be reported along with the results.

Protein expression will be determined by western blot (Fig. 5). In brief, muscle samples will be homogenized in ice-cold lysis buffer. Equal loading of samples (25–40 μg) and transfer efficiency will be monitored with the use of 0.5% Ponceau S staining of the blot membrane. Primary antibodies involved in the insulin signaling pathway (phosphorylated insulin receptor substrate 1 (pIRS-1 Ser 307), phosphorylated protein kinase B (pAkt Ser 473), Akt substrate of 160 kDa (pAS160), phosphorylated 5′ adenosine monophosphate-activated protein kinase (pAMPK Thr 172), and total glucose transporter type 4 (GLUT4)) and oxidative capacity (mitochondrial complexes (OXPHOS)) will be incubated overnight at 4 °C. For each protein, binding of the primary antibody will be detected by peroxidase-conjugated secondary anti-rabbit or anti-mouse antibodies using chemiluminescence detected by ImageQuant LAS 4000 (GE Healthcare®), quantified by densitometry (Scion Image®), and normalized to respective total protein or housekeeping proteins. Potential candidates emerging from RNA-seq analysis will be validated using western blot analysis.

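### RNA-seq reads from human muscle are to be aligned to rn5, a rat assembly; the exploratory non-targeted expression analysis is unsound as written until a human assembly is named.

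*Protocol article*

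**What the plan says.** The patients "will be recruited directly from the Rheumatoid Arthritis Outpatient Clinic of the Rheumatology Division" (Patient recruitment and selection), and they are postmenopausal, so every sample is human. Under Skeletal muscle biopsy, "Percutaneous muscle biopsies will be performed in a random sub-sample of 20 patients at PRE and POST"; the muscle is the vastus lateralis.

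The Non-targeted analysis section extracts RNA from that tissue and sends it to an outside genomics core. On read type: "Sequencing will be carried out using an Illumina HiSeq 2500 platform (Illumina®) with a 50-bp single end reads". On processing: "Alignment to the reference genome (rn5, UCSC), differential expression based on counts per million mapped reads (CPM"), followed by diagnostics. The data go to a public expression repository, and "normalized CPM values for all measured genes will also be provided".

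The Targeted analyses section makes later steps depend on this result: "Potential genes that emerge from the RNA-seq analysis will be validated using qRT-PCR analysis", and "Potential candidates emerging from RNA-seq analysis will be validated using western blot analysis". The same section also lists targets fixed in advance (*LPL*, *PDK4*, *ACACA*, and a set of insulin-signalling and mitochondrial proteins) that do not depend on the sequencing.

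**The concern.** The species of the sample and the species of the reference do not match. In UCSC naming the prefix rn stands for *Rattus norvegicus* and human assemblies carry hg. The article does not spell this out, but it is what the identifier means.

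This is something the article states, not something it leaves to a fuller document. A longer protocol or analysis plan could contradict the sentence, but it could not make a rat build suitable for human reads.

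At stake is the only non-targeted analysis of the muscle tissue. Its output is the list of differentially expressed genes, which selects further genes and proteins for laboratory follow-up, and a public set of expression values that others may reuse. Follow-up by qRT-PCR and western blot can reject a false lead. It cannot recover a gene that the alignment never detected.

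**Working it through.** **1. Passages side by side.** There is no stated figure to reproduce; the check is one of consistency.

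| Item | Protocol article | Section |
|---|---|---|
| Source of RNA | Vastus lateralis of 20 patients, before and after (20 × 2 = up to 40 samples) | Skeletal muscle biopsy |
| Population | Postmenopausal patients with rheumatoid arthritis | Patient recruitment and selection |
| Reference | rn5, UCSC (rat) | Non-targeted analysis |
| Read type | 50 bp, single end | Non-targeted analysis |
| Animal tissue or second, human alignment | None mentioned | Whole article |

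No reading of the text reconciles the second and third rows.

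**2. How many reads could still align?** The article gives neither the aligner's tolerance nor human-rat identity, so both are assumptions here. If each of 50 bases differs independently with probability *d*, and the aligner accepts at most *k* mismatches, the share of reads that can align is

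P(X ≤ k), with X ~ Binomial(50, d).

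For example, with d = 0.10 and k = 2: 0.9^50 + 50(0.1)(0.9^49) + 1225(0.01)(0.9^48) = 0.005 + 0.029 + 0.078 = 0.112.

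| Assumed identity (divergence *d*) | k = 2 | k = 3 | k = 5 |
|---|---|---|---|
| 99.9% (0.001; same species) | about 100% | about 100% | about 100% |
| 95% (0.05) | 54% | 76% | 96% |
| 90% (0.10) | 11% | 25% | 62% |
| 85% (0.15) | 1.4% | 4.6% | 22% |
| 80% (0.20) | 0.1% | 0.6% | 4.8% |

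Over identities of 85% to 95% the share runs from about 1% to 96%. The table shows the direction, and that the loss varies sharply with a gene's conservation. It does not estimate the loss in this study. Independence is also a simplification, since conservation clusters along transcripts.

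**3. What this does to the comparison.** Let p_gi be the true share of gene *g* in sample *i*, and r_g the fraction of its reads that align. Then

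CPM_gi = 10^6 × p_gi r_g / S_i, where S_i = Σ_h p_hi r_h.

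The ratio between two samples is CPM_g1 / CPM_g2 = (p_g1 / p_g2) × (S_2 / S_1). The gene's own factor r_g cancels, because every sample is human and suffers the same loss. What remains is a factor common to all genes, near 1 if the samples have similar overall composition.

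Three things do not cancel:

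- Genes with r_g near 0 drop out altogether.
- Genes with low r_g have fewer counts. The counting part of the standard error of a log fold change grows by about 1/√r: 1/√0.54 = 1.4, 1/√0.112 = 3.0, 1/√0.0142 = 8.4.
- Reads placed on the wrong gene mix two genes' signals, and the cancellation then fails for that gene.

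In addition, CPM values read within a sample, as a user of the public deposit might read them, keep the full distortion by r_g.

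**The case against.** The strongest reply is about consequence. This is an exploratory analysis in 20 patients, far from the primary outcome, which is accelerometer-measured sedentary time. Per-gene loss is shared by all samples and largely cancels in between-group and before-after comparisons. The raw reads survive and can be re-aligned. The identifier may simply have been carried over from an animal protocol, with a human build intended. A very low mapping rate would probably be noticed in the diagnostics that the article plans.

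Most of that stands, and it rules out several stronger conclusions a reader might infer:

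- *Most reads would be lost.* Not supported. This fails at 95% identity even with two mismatches allowed (54% align), and at 90% with five allowed (62%). The article gives neither quantity.
- *The candidates would be wrong, or biased towards one arm.* Not supported as a general statement. The first-order effect is missed genes and weaker sensitivity; false leads through misassignment are possible, but qRT-PCR and western blot could reject them.
- *The biopsy material would be wasted.* Not supported. Four portions are stored, sequencing draws on about 20 mg of tissue, and the tissue also serves the prespecified targeted assays.
- *The trial's results are invalid.* Not supported. Only the non-targeted muscle expression analysis, and what is selected from it, depends on this alignment.

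What the reply does not do is make rn5 right for human reads. Likely detection by the core is no substitute for a correct instruction, and at the milder end of the range the mapping rate might not look alarming.

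**Conclusion.** Wrong as written. A rat assembly is named for human samples, and nothing in the article explains it. Followed literally, the exploratory non-targeted muscle analysis would be unsound: reads from less conserved genes lost or misassigned, genes missed, sensitivity reduced, and annotation to rat genes. The error would pass to the additional candidates chosen for qRT-PCR and western blot and to the publicly released CPM values.

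The size is undetermined from the article. The conclusion rests only on the meaning of the identifier and the human origin of the tissue; the range of about 1% to 96% of reads aligning rests on assumed identity and aligner tolerance. Whether rn5 has been or will be used in practice cannot be told from the text. The primary outcome, clinical outcomes, lipidomics, T cell function and prespecified targeted genes and proteins are not affected.

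**What to change.** In Non-targeted analysis, replace the rn5 reference with a named human assembly and the matching gene annotation, with version (for example UCSC hg38/GRCh38). Before counts are produced, obtain confirmation from the genomics core that its pipeline uses that assembly. If any samples have already been processed against rn5, re-align their raw reads, regenerate the counts and CPM values, and choose follow-up candidates and make the public deposit only from the re-aligned data.

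The cost is one pipeline setting, plus computing time for anything already processed. No new samples, biopsies or sequencing are needed.

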##### Targeted analyses

Gene expression will be determined by qRT-PCR (Fig. 5). In brief, total RNA isolation, quantification, and purity will be carried out as described above. Gene expression will be determined by qRT-PCR analyses using the microglobulin (*B2M*) gene as a housekeeping gene. All qRT-PCR reaction mixtures will be prepared using a Superscript Platinum One-Step kit (Invitrogen, CA, USA) with incorporated Maxima SYBR Green/ROX qPCR Master Mix (Applied Biosystems, CA, USA) on a Step One Thermocycler (Applied Biosystems, CA, USA). The messenger RNA (mRNA) levels of the genes lipoprotein lipase (*LPL*), pyruvate dehydrogenase kinase 4 (*PDK4*), and aetyl-CoA carboxylase alpha (*ACACA*) will be analyzed. Potential genes that emerge from the RNA-seq analysis will be validated using qRT-PCR analysis. Relative change in gene expression (Δ-ΔCq) will be calculated by subtraction of the ΔCq at PRE (used as a calibrator) to the corresponding ΔCq at POST. Finally, fold change will be determined as 2-Δ-ΔCq. All sense and reverse primers used for each gene will be reported along with the results.

Protein expression will be determined by western blot (Fig. 5). In brief, muscle samples will be homogenized in ice-cold lysis buffer. Equal loading of samples (25–40 μg) and transfer efficiency will be monitored with the use of 0.5% Ponceau S staining of the blot membrane. Primary antibodies involved in the insulin signaling pathway (phosphorylated insulin receptor substrate 1 (pIRS-1 Ser 307), phosphorylated protein kinase B (pAkt Ser 473), Akt substrate of 160 kDa (pAS160), phosphorylated 5′ adenosine monophosphate-activated protein kinase (pAMPK Thr 172), and total glucose transporter type 4 (GLUT4)) and oxidative capacity (mitochondrial complexes (OXPHOS)) will be incubated overnight at 4 °C. For each protein, binding of the primary antibody will be detected by peroxidase-conjugated secondary anti-rabbit or anti-mouse antibodies using chemiluminescence detected by ImageQuant LAS 4000 (GE Healthcare®), quantified by densitometry (Scion Image®), and normalized to respective total protein or housekeeping proteins. Potential candidates emerging from RNA-seq analysis will be validated using western blot analysis.

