### Statistical analysis

Data normality will be tested using the Kolmogorov-Smirnov or the Shapiro-Wilk *W* test. Parametric data will be presented as mean ± 95% CI. Non-parametric data will be log-transformed and presented as back-transformed mean ± 95% CI. The ES (Cohen’s *d*) will be calculated and interpreted as small (0.2–0.4), medium (0.5–0.7), or large (≥ 0.8).

Generalized linear mixed model analyses will be performed for each dependent variable, with group and time as fixed factors and patients as a random factor; the models will be adjusted by age, BMI, disease activity, and if different between groups, baseline values of the outcome variable. In the case of significant *F* values, a post-hoc test with Tukey’s adjustment for multiple comparisons will be performed. Analyses will be conducted according to the intention-to-treat principle, in which missing values will be handled by the generalized linear mixed model by using maximum likelihood to estimate the parameters of the model. To test the influence of reducing sedentary time on health-related outcomes, patients will be allocated into “responder” and “non-responder” sub-groups (according to changes in sedentary time); thereafter, the dependent variables will be compared between them.

Data analysis will be performed using the SAS 9.3 (SAS Institute Inc., Cary, NC, USA) for Windows. The level of significance will be set at *p* ≤ 0.050.

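### For qRT-PCR, the fold change calibrated on each patient's own PRE value does not fit the group-and-time mixed model; if the constant PRE is entered as a time level, standard errors for POST means and POST between-arm differences are about 29% too small

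*Protocol article*

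**What the plan says.** Three parts of the protocol article bear on this.

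- **Targeted analyses (qRT-PCR).** B2M is the only reference gene named ("gene as a housekeeping gene"). Relative change "will be calculated by subtraction of the ΔCq at PRE (used as a calibrator) to the corresponding ΔCq at POST". The last step is: "Finally, fold change will be determined as 2-Δ-ΔCq". The targets are LPL, PDK4, ACACA and any genes carried forward from RNA-seq.
- **Skeletal muscle biopsy.** "Percutaneous muscle biopsies will be performed in a random sub-sample of 20 patients at PRE and POST".
- **Statistical analysis.** "Generalized linear mixed model analyses will be performed for each dependent variable, with group and time as fixed factors and patients as a random factor". Covariates are age, BMI, disease activity and, "if different between groups, baseline values of the outcome variable". After a significant F value, "a post-hoc test with Tukey’s adjustment for multiple comparisons will be performed". On scale: "Non-parametric data will be log-transformed and presented as back-transformed mean ± 95% CI".

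For lipid species, the Lipidomics section says that the percentage change from PRE to POST will be compared between groups. Targeted analyses has no corresponding sentence for gene expression.

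**The concern.** A group-and-time model needs an outcome measured at both times. The expression measure as defined has no PRE value that varies: each patient is her own calibrator, so ΔΔCq at PRE is 0 and fold change is 1 by construction. The usual random-intercept model assumes one residual variance for both times. With zero variance at PRE and all variation at POST, it averages the two and understates the variation at POST.

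Two further consequences follow. The rule to adjust for baseline when the groups differ can never apply to this variable, because a constant cannot differ between groups. And log transformation is conditional on a normality test, so with about 10 patients per arm a skewed fold change may stay on its raw scale.

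At stake are the 95% intervals for the qRT-PCR genes and any POST comparison between arms for them.

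**Working it through.** **No stated figure to reproduce.** The article gives no SD, interval width or power for gene expression. The sample size calculation concerns sedentary time and is not an input here.

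**Inputs**
- Calibrator: own PRE ΔCq (Targeted analyses).
- Model: group and time fixed, patient random (Statistical analysis). Assumed: their interaction is included, one residual variance applies to both times, and covariates are left out for simplicity.
- n = 10 per arm: 20 biopsied patients and the 1:1 ratio, assumed to split evenly.
- s² = variance of the log-scale change. It is not given, but it cancels from every ratio on the log scale.

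**Step 1. What the model estimates.** With PRE constant, Var(PRE) = 0, Var(POST) = s² and Cov(PRE, POST) = 0.
- Between-patient mean square: 2 × Var(patient mean) = 2 × s²/4 = s²/2.
- Within-patient mean square: Var(POST − PRE)/2 = s²/2.
- Patient variance: (s²/2 − s²/2)/2 = 0. Residual variance: s²/2.

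**Step 2. Standard errors against the correct values**

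| Quantity | Model | Correct | Ratio |
|---|---|---|---|
| POST arm mean | √(s²/2n) | √(s²/n) | 0.707 |
| POST between-arm difference | √(s²/n) | √(2s²/n) | 0.707 |
| Within-arm change | √(2 × (s²/2)/n) = √(s²/n) | √(s²/n) | 1.00 |
| Group by time | √(4 × (s²/2)/n) = √(2s²/n) | √(2s²/n) | 1.00 |

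So 1 − 1/√2 = 29.3% too small for the first two rows, and no error in the last two. Restricted maximum likelihood fits gave the same 0.707.

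**Step 3. Error rates** (simulation, log scale, no true effect, 10 per arm; 18 df = 20 − 2, 36 df = 40 − 4)

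| | 18 df | 36 df |
|---|---|---|
| Type I error, POST between-arm, unadjusted | 15.4% | 16.7% |
| Implied 95% CI coverage | 84.6% | 83.3% |
| Same contrast, Tukey over four cells | about 6% | about 7% |
| Group-by-time test | about 5.0% | about 5.7% |

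The large-sample coverage is 2Φ(1.96/√2) − 1 = 0.834. For this one pair, Tukey with a correct SE would give only about 1%, so the adjustment absorbs the SE error rather than correcting it.

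**Step 4. The other reading: one change value per patient.** There is no zero-variance cell, and the SE ratio is 1.00. Two weaknesses remain.
- *Skew on the fold scale.* If log2 change is normal with mean 0 and SD σ, the mean fold change is exp((σ ln 2)²/2). For assumed σ of 0.5, 1.0 and 1.5 this is 1.06, 1.27 and 1.72, although the typical patient has not changed. With equal σ in both arms it cancels between arms but not within an arm.
- *Unused baseline.* If ΔCq has equal variance at both times and correlation ρ, the variance of the between-arm estimate from POST adjusted for PRE, relative to the change score, is (1 − ρ²)/(2(1 − ρ)) = (1 + ρ)/2, ignoring the one df spent. For assumed ρ of 0.3 to 0.7 that is 0.65 to 0.85.

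**The case against.** The strongest reply is that the article never says a constant PRE will be fed to the model. Targeted analyses defines one number per patient, and the team compares a change score between groups for lipids. On that reading nothing is narrowed. This stands, and it makes the 29% conditional. It does not remove the mismatch: the model is stated for every dependent variable, and the lipid sentence shows that the authors wrote an exception where they wanted one.

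Second, even on the unfavourable reading, the test of interest survives. Group-by-time and within-arm change have correct SEs, and post-hoc tests follow only a significant F with Tukey adjustment. With the interaction F as gate, the POST between-arm false-positive rate returns to about 5.0 to 5.7%. This also stands. What remains exposed is the displayed intervals for POST means and unadjusted POST differences, because interval reporting is not gated by F.

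Third, the normality rule would send marked skew to a log scale. That is partly right, but a normality test on about 10 per arm does not guarantee it.

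A reader might also infer that B2M alone makes the gene results unreliable. A B2M shift of 0.25, 0.5 or 1 cycle would multiply every target by 1.19, 1.41 or 2.00, but those shifts are hypothetical. Nothing in the article shows that B2M moves in these patients, and a shift equal in both arms cancels in the randomised comparison. RNA-seq and western blot in the same plan do not depend on B2M mRNA.

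**Conclusion.** The point holds as an inconsistency between two sections, with a conditional numerical consequence. If the PRE-fixed measure is entered at both times with a common variance, SEs for POST means and POST between-arm differences are 29% too small, and unadjusted 95% intervals cover about 83 to 85%. This rests on 10 patients per arm, an interaction term in the model and no covariates; on the log scale it does not depend on the unknown SD.

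It would go too far to conclude that the planned test of the intervention on gene expression is invalid, or that the reported intervals will certainly be wrong. The group-by-time contrast is sound on either reading, and the text does not fix which reading applies. The endpoint is mechanistic and confined to the biopsy sub-sample of 20; the primary outcome is untouched. It still merits correction, because analysing ΔCq improves on both readings.

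**What to change.** In Statistical analysis or Targeted analyses, state for qRT-PCR that:

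1. the dependent variable is ΔCq, which is already a log-scale quantity, and no normality test decides the scale;
2. the between-arm difference is estimated with PRE ΔCq retained, either with PRE and POST ΔCq both in the mixed model and the group-by-time contrast as the effect, or with POST ΔCq adjusted for PRE ΔCq whether or not the groups differ at baseline;
3. 2^-ΔΔCq is reported only as the back-transformed contrast with its 95% CI.

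This removes the zero-variance cell and the raw-scale skew, and it uses a baseline already measured. With a valid variance for POST, the SE ratio is 1.00, coverage is about 95% and type I error about 5%.

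Optionally, use the RNA-seq already planned on the same biopsies to check that B2M is stable by arm and time. Extra reference genes are not required.

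The cost is a few sentences of analysis wording: no new samples and no new assays.
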